**Methods/Design:**

In this randomised controlled trial, family carers of older patients aged 70+ discharged from a Medical Assessment Unit in a Western Australian tertiary hospital, plus the patients themselves, will be recruited at discharge (*N* = 180 dyads). Carers will be randomly assigned (block allocation, assessors blinded) to receive usual care (control) or the new program (intervention). The primary outcome is the carer’s self-reported preparedness for caregiving (Preparedness for Caregiving Scale administered within 4 days of discharge, 2–3 weeks post-discharge, 6 weeks post-discharge). To detect a clinically meaningful change of two points with 80 % power, 126 carers need to complete the study. Patients’ returns to hospital and subsequent length of stay will be ascertained for a minimum of 3 months after the index admission. Regression analyses will be used to determine differences in carer and patient outcomes over time associated with the group (intervention or control). Data will be analysed using an Intention to Treat approach. A qualitative exploration will examine patients’ and their family carers’ experiences of the new program (interviews) and explore the hospital staff’s perceptions (focus groups). Process evaluation will identify barriers to, and facilitators of, program implementation. A comprehensive economic evaluation will determine cost consequences.

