In parallel work in community palliative care in the United Kingdom, a need for a systematic and effective carer needs assessment process was identified. The Carer Support Needs Assessment Tool (CSNAT) was developed following extensive reviews of the literature [10–12], and from interviews with bereaved carers [13]. The tool was subsequently validated using a sample of 225 current carers [14]. The CSNAT is a brief tool, yet covers all identified support need areas. Each item represents a core carer support domain in home care. The items fall into two sets: those that enable the carer to care for the patient at home and those that enable direct support for the carer [13]. The CSNAT has recently been used in a Western Australian study in palliative home care; it was reported to be practical and useful; to prompt carers to consider their own needs rather than just those of the patient; to validate, reassure, and empower carers; and to help carers access the support that they need [15].

The aim of this study is to determine how implementing an evidence-based, systematic, and targeted support program for family carers of older patients - immediately after the patient’s discharge from a metropolitan Western Australian hospital’s MAU - impacts upon these carers; the patients for whom they provide care; and costs to WA Health, the local health care system. The program being evaluated is termed the Further Enabling Care at Home (FECH) program, and it uses the CSNAT to identify and prioritise family carers’ support needs that are subsequently addressed. The study has three hypotheses:H1: That the enhanced support of family carers facilitated by the FECH program will prepare families to sustain their caregiving role better than usual care.H2: That, because family carer roles are better supported, implementation of this program will reduce (a) patients’ re-presentations and readmissions to hospital within 3 months of discharge, and (b) length of hospital stay when readmissions do occur.H3: That reduced costs to WA Health will outweigh costs of implementing the program.

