### Carer outcome and data collection

#### Primary outcome variable

The primary outcome is preparedness for caregiving, to be measured with the Preparedness for Caregiving Scale (PCS) from the Family Care Inventory [19] (T1- T3). This measure is an 8-item scale, with five response options (0 = not at all prepared, 4 = very well prepared) and is designed for use with carers of older people receiving homecare or experiencing care transitions. Construct validity has been established in older people, and the measure has been shown to be reliable (Cronbach’s alpha coefficients: 0.88-0.93) [19]. Testing in patients with a life threatening illness confirmed satisfactory internal consistency reliability as well as unidimensionality [20].

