### Statistical analysis

Data analyses will be performed using the IBM SPSS statistical software package [31]. A p-value of <0.05 will be taken to indicate a statistically significant result in all tests.

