#### Carer outcome

Outcome analysis will be conducted using an Intention to Treat approach. The change in the total Preparedness for Caregiving Scale [19] score between T1 and T3 will be calculated for each carer. An initial *t*-test will compare changes between treatment groups. If changes in scores are not normally distributed, a non-parametric method will be used instead (Wilcoxon 2-sample test). In the (unlikely) event that groups differ on the basis of baseline variables, a regression model will be used instead of the *t*-test, so that these potentially confounding variables can be taken into account. A random effects regression model will be used to examine changes in the Preparedness for Caregiving Scale score over all three data collection periods (instead of just baseline/end of study). This model will be used so that correlations between measurements made on the same participants can be taken into account. Results of the model will help show whether changes in scores happen soon after recruitment, or later. The model can be extended to adjust for other potentially confounding variables.

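### The analysis that decides H1 is not fixed: preparedness has no primary time point and is analysed both as T1–T3 change and in a three-time-point model, each at p<0.05

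*Protocol article*

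**What the plan says.** H1, in the Background, is that the program "will prepare families to sustain their caregiving role better than usual care". It names no time. The abstract gives the primary outcome as the "Preparedness for Caregiving Scale administered within 4 days of discharge, 2–3 weeks post-discharge, 6 weeks post-discharge", and the Primary outcome variable section likewise lists T1 to T3 without singling one out.

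The Carer outcome section describes two analyses of this outcome:

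- A change score: "The change in the total Preparedness for Caregiving Scale [19] score between T1 and T3 will be calculated for each carer". An initial t-test compares it between groups. A Wilcoxon test replaces the t-test if changes are not normal, and a regression replaces it if the groups differ at baseline.
- A longitudinal model: "A random effects regression model will be used to examine changes in the Preparedness for Caregiving Scale score over all three data collection periods". It is set against a comparison of baseline and end of study alone. Its stated use is to help show whether change comes early or late.

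The Statistical analysis section adds: "A p-value of <0.05 will be taken to indicate a statistically significant result in all tests". The abstract's description of the analysis refers to regression for group differences over time and does not mention the t-test. The Sample size section is built on a two-point change in the total score and does not say over which interval.

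**The concern.** A confirmatory hypothesis needs one contrast, fixed in advance, whose result decides it. Here two analyses bear on H1, and nothing says which prevails if they disagree. The Carer outcome section puts the T1–T3 comparison first, but the word *initial* does not make it decisive. The abstract points to the longitudinal regression.

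Disagreement is plausible. The last program contact falls within 14 days of discharge. T2, at 2–3 weeks, comes at or just after the end of the program, and T3, at 6 weeks, about a month after it. A joint test over time and a T1–T3 comparison respond differently to a benefit that appears early and fades.

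The two analyses may also use different carers. A T1–T3 change exists only for carers measured at both times, and about 30% attrition is expected. A random effects model can use carers who gave T1 and T2 but not T3.

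**Working it through.** **1. What the sample size pays for.** Inputs from the Sample size section: difference 2 points on the total score, SD of change about 0.5 in mean score, power 80%, attrition about 30%. The Primary outcome variable section gives 8 items. Reading the SD per item, the SD on the total score is 8 × 0.5 = 4.0 (an assumption; an SD of 0.5 on the total score would need only 1 carer per group). Two-sided 5% is also assumed, since sidedness is not stated.

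n per group = 2 × (1.960 + 0.842)² × 4² / 2² = 62.8, so 63.

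Total completing = 2 × 63 = 126; recruited = 126 / 0.70 = 180.

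Both stated figures are reproduced, with power 80.1% at 63 per group. One-sided 5% would give 50 per group. The trial is therefore sized for a single two-sided 5% comparison of change.

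**2. Which contrast that is.** The places that could settle it, side by side:

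| Place | What it points to |
|---|---|
| H1 | no time point |
| Primary outcome (abstract and methods) | T1, T2 and T3 |
| Abstract, analysis | regression over time |
| Sample size | a change, interval not stated; 126 carers completing |
| Carer outcome, first analysis | T1–T3 change |
| Carer outcome, second analysis | all three times; use is timing of change |

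T1–T3 has the best support: it is the only contrast explicitly calculated, and carers who complete the study most naturally means those who reach T3. No section declares it the test of H1.

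**3. Error rate if the model could also count as success.** Suppose H1 could be claimed either from the T1–T3 test or from the model's joint group-by-time test (2 degrees of freedom). Let z₂ and z₃ be the standardised group differences in T1–T2 and T1–T3 change, with correlation r and no true effect. The joint statistic is

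W = z₃² + (z₂ − r z₃)² / (1 − r²) = z₃² + u²,

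where u is standard normal and independent of z₃. Then

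P(|z₃| > 1.960 or W > 5.991) = 1 − P(|z₃| ≤ 1.960 and z₃² + u² ≤ 5.991) = 0.075.

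Numerical integration gives 0.0751. Simulation with 1,000,000 draws gives 0.0751, 0.0754, 0.0749 and 0.0751 at r = 0.3, 0.5, 0.7 and 0.8. The result does not depend on r, which the document does not give. It is a large-sample figure and treats both tests as using the same carers.

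**4. If the model's T3 term were used instead.** That term estimates nearly the same quantity as the T1–T3 comparison, so counting either would add little to 5%. The 7.5% therefore applies to the joint-test reading only.

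**5. After the fix.** With one declared contrast the error rate is 5%. At 63 completers per group the power is 80.1%, so 180 recruited remains right on the plan's own inputs.

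**The case against.** The best defence is that the plan already has a primary analysis in all but name. One per-carer variable is calculated and one between-group test of it is described; the Wilcoxon test and the regression are substitutes for that test, not additions. The sample size budgets for one comparison among carers who complete the study. The model is given a descriptive job, to show when change happens. The source is also a condensed article, and details such as the coding of time or the model term to be tested may sit in a fuller document that is not shown.

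Most of this stands. It makes T1–T3 the natural candidate, and the unnamed model term is not a fault of an article in itself. It does not fully answer the point. The time point and contrast are part of the primary outcome's definition, the article goes into analysis detail without settling them, and its abstract describes a different main analysis from the one listed first in the methods.

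A reader might go further and infer that a benefit at T2 alone could be claimed as success, with a false-positive rate of 9–10%. The document does not support that. It plans no separate T2 group test, and figures of that size require one. Nor does it state any intention to choose between analyses after seeing the data; it only leaves the choice open.

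**Conclusion.** The point holds in a limited form. The deciding analysis for H1 is not fixed: no primary time point is named, two analyses of the primary outcome share the 5% threshold, and abstract and methods point to different ones. The T1–T3 change is implied as primary and the model as supportive, but this has to be inferred.

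The size is moderate. If a joint group-by-time test could also establish H1, the false-positive rate is about 7.5% against 5%. This rests on the assumption that the joint test is used and treated as confirmatory, which the document neither states nor excludes. If the T1–T3 contrast alone decides, there is no inflation and the gap is one of declaration. It still deserves correction, because a single declared contrast removes a choice that could otherwise be made with results in hand. Estimating it from the model also suits the stated intention-to-treat approach better than a change score that drops carers without T3.

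**What to change.** In the abstract, Sample size and Carer outcome sections:

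- Name the between-group difference in PCS total change from T1 to T3 (6 weeks) as the single test of H1, two-sided 5%.
- Estimate it as the T3 group-by-time term of the random effects model with time as a category, so that carers with partial follow-up are kept.
- Report the t-test of T1–T3 change as a sensitivity analysis.
- Call the T2 contrast secondary. It describes timing and cannot by itself support H1.
- Say that the two-point difference in the sample size refers to the T1–T3 change.

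The cost is a few sentences. No data collection changes and recruitment stays at 180. What is given up is the possibility of confirming H1 on an effect seen only at T2.

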#### Patient outcomes

Patient outcomes will be compared between groups using t-tests or regression models. For example, the total length of hospital stay will be calculated and compared between groups using a *t*-test (after log-transformation of the data if indicated). Number of re-admissions to hospital or presentations to ED will be compared using the same method. A regression model will be used to take into account potentially confounding variables (if relevant). The association between change in preparedness and change in health care utilisation will be evaluated using carer outcomes linked to the administrative data.

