### Patient outcomes and data collection

Quantitative patient outcome data will address Western Australian health care system utilisation and will be obtained through linked administrative health data provided via the WA Data Linkage System (WADLS) [28]. These Data Linkage Unit (DLU) data will capture reason for service and mode of transport plus: date of service, symptom/presenting problem, and triage code (ED presentation); admission and separation dates, primary diagnosis code, co-diagnosis code, and diagnosis related group (hospitalisation data). In addition, to account for time at risk, and to capture deaths resulting from acute events during the study follow-up period, date and cause of death will be collected.

The data retrieved from data linkage will cover the time period from the date of the index separation of the patient whose carer is the first to be recruited to the study until 3 months after the index separation of the patient whose carer is the last to be recruited. Since recruitment is planned to last approximately 6 months, this time period will cover approximately 9 months.

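### The stated analysis of re-admissions, ED presentations and hospital days has a log step that is undefined for patients with no return, and no place for the time at risk that the trial collects

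*Protocol article*

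**What the plan says.** Protocol article, Statistical analysis, Patient outcomes:
- The opening sentence allows two routes: "Patient outcomes will be compared between groups using t-tests or regression models".
- The worked example is hospital days: "the total length of hospital stay will be calculated and compared between groups using a" t-test, "after log-transformation of the data if indicated".
- The counts follow: "Number of re-admissions to hospital or presentations to ED will be compared using the same method".
- The only purpose then given for a regression model is adjustment for confounders. No model type, exposure term or rule for zeros is stated.

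Patient outcomes and data collection: dates and causes of death are obtained "to account for time at risk, and to capture deaths resulting from acute events during the study follow-up period".

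The follow-up period is given in three ways. Hypothesis H2 (Background) uses 3 months from discharge. The study objectives use 3 months or more. The data-linkage request runs about 9 months in calendar time, from the first patient's index separation to 3 months after the last patient's.

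The stay to be compared is given in two ways. H2(b) concerns "length of hospital stay when readmissions do occur", while the analysis section refers to total stay.

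**The concern.** Three things do not fit together.

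1. **The log step.** H2(b) itself shows that some patients are expected not to return. They have zero re-admissions and zero days, and often zero ED presentations. A log transformation cannot be applied to them. For the carer outcome the article gives a rank test as fallback; here the log is the only stated remedy for non-normal data. The analyst would have to choose between adding a constant and dropping patients, possibly after seeing the data.
2. **Time at risk.** Death dates are requested for a stated purpose, yet a t-test on counts or days has no exposure term. A patient who dies soon after discharge is recorded as having few or no returns.
3. **The window and the stay.** If all linked data are used, follow-up runs from 3 to about 9 months depending on recruitment date. Stay among the readmitted is a different quantity from total stay per randomised patient.

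What is at stake is the test of H2: whether the program reduces returns to hospital and time spent there.

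**Working it through.** **Inputs from the article.** 180 dyads at about 1:1, so about 90 per arm; significance at p < 0.05 (two-sided assumed). The article gives no sample size, event rate or mortality for patient outcomes, so there is no figure of its own to reproduce on this point.

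**Assumptions.** Counts are negative binomial with dispersion 1. The mean is 0.5 or 0.8 events per patient per 3 months. Deaths are 10% per 3 months in both arms, or 15% control against 5% intervention. Follow-up is either a fixed 3 months or spread uniformly over 3 to 9 months. Each scenario has 2000 simulated trials of 90 per arm; the negative binomial model could be fitted in 98.7% to 99.8% of them.

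**Step 1: how many zeros.** For mean m, P(0) = exp(−m) under Poisson and 1/(1+m) under negative binomial with dispersion 1.
- m = 0.3: exp(−0.3) = 74%; 1/1.3 = 77%.
- m = 1.2: exp(−1.2) = 30%; 1/2.2 = 45%.

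Over this range 30% to 77% of patients have no defined log value.

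**Step 2: error and power with equal deaths (10% per 3 months).**

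| Method for counts | Error, m = 0.5, fixed 3 months | Power, rate ratio 0.6, m = 0.5, fixed 3 months | Power, rate ratio 0.6, m = 0.8, 3–9 months |
|---|---|---|---|
| t-test, untransformed | 5.0% | 40% | 62% |
| t-test on log(1+y) | 4.8% | 39% | 58% |
| t-test on log(y), zeros dropped | 5.9% | 12% | 33% |
| Negative binomial, time offset | 5.2% | 41% | 68% |

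Dropping zeros is the damaging choice. The untransformed t-test holds its error rate and loses about 1 point of power at a fixed 3 months and about 6 points when follow-up varies.

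**Step 3: time at risk when mortality differs and there is no true rate effect.** Take 3 months as the time unit and let d be the probability of death per unit, so the hazard is h = −ln(1−d). Mean time at risk over one unit is d/h.
- Control, d = 0.15: h = 0.1625; 0.15/0.1625 = 0.923.
- Intervention, d = 0.05: h = 0.0513; 0.05/0.0513 = 0.975.
- Ratio 0.975/0.923 = 1.06.

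For follow-up uniform on 1 to 3 units, mean time at risk is [1 − (e^(−h) − e^(−3h))/(2h)]/h.
- Control: (1 − 0.7257)/0.1625 = 1.688.
- Intervention: (1 − 0.9029)/0.0513 = 1.893.
- Ratio 1.893/1.688 = 1.12.

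The simulated median ratios of mean counts were 1.07 and 1.13, in line with these values. The arm with fewer deaths looks worse. The t-test's error was 5.4% at 3 months and 8.0% over 3 to 9 months (log(1+y): 5.9% and 9.1%). With the offset the median rate ratio was 1.00 to 1.01 and the error 5.3% to 5.5%.

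**Step 4: stay among the readmitted.** A constructed example assumes 35% readmitted, lognormal stays (median 4 days, log-SD 0.9), and a program that mainly averts short stays. Readmission falls from 35% to 26.1% and days per patient from 2.09 to 1.87, yet mean stay among the readmitted rises from 5.99 to 7.17 days. This shows that the two quantities can move in opposite directions; it does not estimate what would happen in this trial.

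**The case against.** - **The t-test itself is not broken.** A reader might infer that the stated analysis fails because of the zeros. It does not: kept untransformed, the t-test has 5.0% error and almost the same power as the count model under balanced exposure. This stands.
- **Nobody is dropped by the text.** A reader might infer that the log step removes patients with no return. The article never says so, and the transformation applies only if indicated. An analyst could leave the data untransformed or add a constant. For counts, log(1+y) costs little. For days it had slightly more power than the untransformed t-test (33% against 27%, rate ratio 0.6, fixed 3 months). This stands as to size. The choice is still left open, and the result then depends on the constant.
- **Regression is allowed.** The section's opening sentence and the Abstract both mention it, and the t-test is introduced as an example. A journal article may leave model details to a fuller plan. This stands in part: the article nevertheless commits the counts to the t-test method, and the section ties regression only to confounders.
- **Time at risk is mentioned.** The purpose is stated where the data are described, so the gap is between that purpose and the stated test. Within a fixed 3 months the effect on error is small even under a large mortality difference (5.4%). This stands.
- **H3.** A reader might infer that the cost hypothesis rests on these tests. It does not: the economic sections cost utilisation separately and use cost-consequence and decision-tree analysis with sensitivity analyses.

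**Conclusion.** The concern holds in a limited form, at moderate severity. The stated log-transformed t-test cannot be run on patients with no return, the article gives no rule for them, and the stated test does not use the time at risk for which death dates are collected. The follow-up window and the definition of stay also need to be reconciled between the hypothesis, the objectives, the data request and the analysis.

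The damage depends on what is done. It is small if zeros are kept, the window is a fixed 3 months and deaths are balanced. It is serious for power if zeros are dropped (12% against 40%). It is a bias if mortality differs by arm: null ratio about 1.07 at 3 months, and about 1.13 with error of 8% to 9% if follow-up also varies from 3 to 9 months. All these sizes rest on assumed event rates, dispersion and mortality; that some patients will have zeros does not.

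The point concerns H2 only. The primary outcome, carer preparedness, is unaffected.

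**What to change.** 1. Remove the log-transformed t-test for these outcomes.
2. Define one window for H2, the 3 months already in the hypothesis, and align the objectives and analysis section with it.
3. Analyse re-admissions and ED presentations by negative binomial regression with log(days alive in the window) as offset, reporting rate ratios with 95% confidence intervals.
4. Compare total hospital days in all randomised patients, zeros included and untransformed, by mean difference with a bootstrap confidence interval.
5. Report deaths by arm beside these results. The mean difference in days is not adjusted for exposure and must be read with them.
6. Align H2(b) with the total stay named in the analysis section, and keep stay among the readmitted as descriptive.

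**Cost.** Only wording changes, since the needed dates are already requested. A rate ratio replaces a mean difference for the counts. For days, leaving the data untransformed may give up a little power (27% against 33% for the untransformed and log(1+y) t-tests in the 3-month scenario), in exchange for a difference in days per patient that is directly interpretable.
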